#### Intervention

All sessions of psychotherapeutic consultation at work will be conducted by licenced psychological or medical psychotherapists or by psychological or medical psychotherapists being in an advanced state of postgraduate training for psychotherapy. The intervention consists of three modules. The first module includes one session of basic diagnostic assessment on mental health (Module 1-A) and one session of work-related diagnostic assessment (Module 1-B). Whereas Module 1-A will be offered to the intervention and control group, Module 1-B and all other modules will exclusively be offered to the intervention group. Based on mental health assessment, participants of the control group will receive recommendations for treatment in CAU (e.g. in- or outpatient acute care, inpatient vocational rehabilitation). Participants of the intervention group will be transferred to CAU if outpatient work-related treatment would not sufficiently cover the individual need for treatment or will receive Module 2. In case participants of the intervention group are transferred to CAU, potential waiting times for treatment will be bridged by Module 2. Module 2 will include up to ten sessions of work-related psychotherapeutic consultation or treatment. Participants of the intervention group with an inability to work will receive further psychotherapeutic consultation during their RTW process in up to five sessions during Module 3. Participants of the intervention group may thus receive up to 17 sessions of psychotherapeutic consultation (Module 1-A: one session; Module 1-B: one session; Module 2: ten sessions; Module 3: five sessions). For both, the control and intervention group, a medical report will be prepared. Participants of the intervention group who received up to four sessions of psychotherapeutic consultation and participants of the control group will receive a follow-up call by study therapists twelve weeks after their last visit. In this call, participants will be asked on how they have coped so far and whether further help regarding treatment in CAU is needed. For all other participants, an equal follow-up will be performed during their last session of psychotherapeutic consultation.

A schematic overview of the intervention is given in Fig. 1 and all its components are further described below.

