##### Module 2. Work-related psychotherapeutic intervention

During module 2, an adaption of the manual from Bode et al. [33] will be used to conduct work-related psychotherapeutic consultation. This will include
Psychoeducation providing information on the relations between work and mental healthFormation of an individual exploratory model of current psychosomatic symptoms. In this model, stressors and resources at work will be includedUsing communication techniques to increase, maintain or restore motivation to workDefining achievable tasks as well as focusing on achievements and resources at work to promote self-efficacyDiscussing problems at work, elaboration of solution approaches and searching for contact persons at work to implement those solution approachesEvaluation and treatment of work-related symptoms (e.g. anxiety or overload) by using cognitive restructuring methodsImplementation of work-related cognitive-behavioural therapeutic treatment measures: resource activating measures, relaxation techniques that can be used at the workplace, coaching of social competences, communication exercises, acceptance of unchangeable situations, clarification of intrapersonal conflicts, promotion of acceptance and emotional competenceDetection of work-related risk factors for development and deterioration of CMDs (e.g. shift work) and giving recommendations of setting-based prevention measures to minimise them

Depending on severity of symptoms, psychotherapeutic consultation during module 2 may either include more curative or preventive aspects. Therefore, module 2 is subdivided into module 2-A comprising work-related short-term psychotherapy and module 2-B comprising work-related prevention. Module 2-A contains both disorder specific psychotherapeutic interventions and the above mentioned work-related interventions. Participants with an ICD-10 diagnosis will thus receive module 2-A and participants with subclinical psychosomatic symptoms without an ICD-10 diagnosis will receive module 2-B.

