#### Discontinuation and modifications of the intervention protocol

The intervention might be discontinued if symptoms decrease and there is no indication for further treatment. If an appointment has been missed, efforts will be made to contact the participant to schedule a new appointment. However, in case that a participant refuses further treatment, the intervention will be discontinued and participants will be asked for their reasons for refusal. If symptoms increase, the psychotherapist and possibly supervisor (i.e. a versed psychotherapist) will weight up further treatment needs. They might schedule a higher frequency of therapy sessions - but no more than 10 sessions of module 2 and 5 sessions of module 3 - or might refer participants to inpatient care. In each case, participants will remain in the study and will be reminded of the follow-up measurements in their last therapy session.

If participants withdraw their informed consent to participate in the study, further therapy sessions will be cancelled. In this case, follow-up measurements will not be performed. If participants also withdraw their informed consent of data storage, collected data of those participants will be deleted and not be included within data analysis.

In general, concomitant care and interventions (e.g. outpatient psychiatric or neurological treatment, somatic treatment, non-medical practitioner treatment, psychological coaching, use of helplines and helpdesks at work) are not prohibited during the trial. Moreover, module 2 aims to bridge waiting times on CAU and therefore also outpatient psychotherapeutic and inpatient psychotherapeutic, psychiatric or rehabilitation treatment are not prohibited during the trial. However, the intervention will be terminated or paused during CAU. Employees receiving psychotherapeutic treatment before starting the intervention are excluded from the study.

In general, discontinuation and all deviations of the intervention protocol will be documented.

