### Assignment of interventions

#### Allocation

Eligible participants will be allocated concealed by randomisation using a centralized web based tool (www.randomizer.at) after Module 1-A. Stratification by centre, days of sickness absence within the last 6 months (< 21 days vs. ≥ 21 days) and level of depression measured by the Patient Health Questionnaire-9 (PHQ-9 [54, 55]; ≤ 10 vs. > 10) using block randomisation of variable sizes will be performed.

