#### Statistical methods

The treatment effect on the primary outcome (days of sickness absence within the last 6 months at the second follow-up) will be analysed using a mixed negative binomial regression model. Treatment group, days of sickness absence within the last 6 months before baseline, gender, age, subjective work ability at baseline as well as the centre will be included as covariates and the respective company as random effect. The primary analysis will be conducted based on the full analysis set according to the intention-to-treat (ITT) principle (i.e. all patients will be analysed in the group they were randomised to).

Missing data for the primary and secondary outcome analysis is assumed to be “missing at random” and replaced using multiple imputation based on predictive mean matching using the covariates of the primary and secondary outcome analysis as potential predictors [75].

As a sensitivity analysis, an evaluation based on the per-protocol (PP) population will be performed. The PP set consists of all participants without major protocol violations. For this analysis, no imputation of missing data will be performed.

In case of significance of the ITT analysis of the primary outcome (two-sided confidence level of 5%), a hierarchical linear mixed model will be used to analyse treatment effects on self-efficacy. This model will include treatment group, self-efficacy at baseline, gender, age, subjective work ability at baseline as well as the centre as covariates and company as random effect. Applying this hierarchical testing strategy, the overall type I error rate will still be controlled.

If no significance of the ITT analysis is achieved, the results of this analysis will be interpreted only in a descriptive sense.

Furthermore, subgroup analyses will be performed to evaluate the role of additional variables (e.g. indication of treatment, type of treatment, symptom severity) on treatment effects on the primary and secondary outcome.

Further collected data (see Table 1) will be analysed using appropriate descriptive methods.

Details of the statistical analysis will be further determined in a statistical analysis plan which will be written before database closure.

All those analyses will be conducted using SAS 9.4 or higher.

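### The subgroup variable 'type of treatment' is not restricted to characteristics fixed before randomisation, so subgroup effects by treatment received would be confounded by prognosis

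*Protocol article*

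**What the plan says.** The Statistical methods section commits to the following for the primary and secondary outcome: "subgroup analyses will be performed to evaluate the role of additional variables (e.g. indication of treatment, type of treatment, symptom severity) on treatment effects". The three variables are examples, and none is defined there.

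Other sections show when and how treatment is determined.

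- **Allocation:** "Eligible participants will be allocated concealed by randomisation using a centralized web based tool (www.randomizer.at) after Module 1-A".
- **Intervention, access to modules:** "Module 1-B and all other modules will exclusively be offered to the intervention group".
- **Intervention, transfer to CAU:** "Participants of the intervention group will be transferred to CAU if outpatient work-related treatment would not sufficiently cover the individual need for treatment".
- **Intervention, Module 3:** "Participants of the intervention group with an inability to work will receive further psychotherapeutic consultation during their RTW process". The Module 3 section describes the recipients as participants with prior sickness absence.
- **Module 2:** "Participants with an ICD-10 diagnosis will thus receive module 2-A and participants with subclinical psychosomatic symptoms without an ICD-10 diagnosis will receive module 2-B".
- **Discontinuation and modifications:** treatment may end when symptoms ease. If they worsen, sessions may become more frequent or the participant may be referred to inpatient care. In addition, "outpatient psychotherapeutic and inpatient psychotherapeutic, psychiatric or rehabilitation treatment are not prohibited during the trial", and the intervention stops or pauses while such care is given.

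The Blinding section states that all baseline variables are collected before allocation. Table 1 lists diagnosis and indication of treatment for all participants.

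**The concern.** A treatment effect within a subgroup is a randomised comparison only if membership can be established in both arms in the same way and cannot be influenced by the allocated treatment. The treatment a participant goes on to receive generally meets neither condition here. If subgroups are formed on it, participants selected for a pathway because of how they are doing are compared either with controls who were never so selected, or with controls selected by a process that allocation itself may have changed.

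At stake is the reading of the module-level results. A pathway reserved for people unable to work would tend to show more absence days than the control group, and a pathway for people who recover quickly would tend to show fewer, even if the intervention worked equally well in both or not at all. Readers would take this as evidence about which components work and for whom.

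**Working it through.** The protocol states no figure on this point, so there is none to reproduce. The check has two parts.

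**1. Is each possible meaning of 'type of treatment' fixed before allocation and present in both arms?**

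| Possible meaning | Determined by | Fixed before allocation? | Identifiable in controls? |
|---|---|---|---|
| Module 2-A or 2-B, as assigned | ICD-10 diagnosis or subclinical status, assessed in Module 1-A | Yes | Yes, through diagnosis status |
| Module 3 received | Inability to work, prior absence | No | No, module not offered |
| Transfer to CAU | Judgement of individual need, in the intervention group | No | No equivalent decision |
| Number of sessions, early end | Symptom course, refusal | No | No |
| CAU treatment taken up | Access, need, interplay with the intervention | No | Yes, but uptake can be changed by allocation |

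One of the five meanings gives a valid subgroup. The protocol text does not limit the term to that one. It also lists indication of treatment as a separate item in the same sentence, which makes treatment received the natural reading.

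**2. How large could the distortion be?**

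The protocol gives no information on how strongly prognosis drives routing, so every input here is an assumption except the starting mean of 36 days per 6 months (Sample size calculations).

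- There is no treatment effect: the true rate ratio is 1.00 for everyone.
- Prognosis S is standard normal in both arms. Expected days are 36 × exp(0.5·S − 0.125), which average 36.
- In the intervention arm, the probability of the more intensive pathway is 1 / (1 + exp(0.85 − b·S)), with b = 0, 0.5 or 1.0.
- Each pathway is compared with all controls.

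The factor exp(0.5·S − 0.125) shifts the distribution of S from mean 0 to mean 0.5. Write P0 for the share routed to the intensive pathway when S has mean 0, and P1 for the share when S has mean 0.5. Then:

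- apparent rate ratio, intensive pathway = P1 / P0
- apparent rate ratio, other pathway = (1 − P1) / (1 − P0)

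| b | P0 | P1 | Intensive | Other |
|---|---|---|---|---|
| 0 | 0.299 | 0.299 | 1.00 | 1.00 |
| 0.5 | 0.309 | 0.362 | 0.362/0.309 = 1.17 | 0.638/0.691 = 0.92 |
| 1.0 | 0.331 | 0.428 | 0.428/0.331 = 1.30 (unrounded inputs) | 0.572/0.669 = 0.85 |

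The overall comparison is 1.00 in each row, since P0·(P1/P0) + (1 − P0)·(1 − P1)/(1 − P0) = 1. A simulation of 1,000 trials with 260 per arm and negative binomial counts agrees: 1.17 and 0.92 for b = 0.5, and 1.28 and 0.86 for b = 1.0.

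The ratios of expected values do not depend on the dispersion. The assumed prognostic spread is compatible with the planning standard deviation of 35 days: the standard deviation of the expected days is 36 × √(exp(0.25) − 1) = 19.2.

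**The case against.** The strongest reply is that the term is undefined. Module 2-A is short-term psychotherapy and Module 2-B is prevention, which could fairly be called two types of treatment. They are assigned by diagnosis status, known for everyone before allocation, and on that reading the subgroup is sound. The protocol also defers details to an analysis plan written before database closure, describes no comparison of each module with all controls, and keeps these analyses outside the confirmatory sequence.

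Much of this stands. The 2-A/2-B split is valid and should be kept, and the point is of secondary weight. The deferral does not remove it, however. The protocol does more than leave a detail open: it names a variable as a modifier of the treatment effect, and most meanings of that variable are unsuitable whatever model is used.

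Three stronger readings are not supported.

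- **That Module 3 is given on the basis of the outcome itself.** The primary outcome is absence in the six months before the 15-month follow-up. Inability to work or prior absence that leads to Module 3 is prognostic for that outcome but is not the same quantity.
- **That the module-level results would drive the financing of modules 1 and 2 versus module 3.** The Discussion bases that division on social law, and ties implementation to overall effectiveness and the economic evaluation.
- **That the distortion must be dramatic.** Suppose 30% of the intervention group averaged 60 days and the rest 11.4, which gives the planned mean of 26. With a common rate ratio of 26/42 = 0.62, the matching control strata would average about 97 and 18 days. Their between-stratum standard deviation alone would be √(0.3 × 0.7) × (96.9 − 18.4) = 36 days, more than the planned total of 35. So extreme a split does not fit the protocol's assumptions.

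**Conclusion.** The point holds with limits. As written, the protocol allows treatment effects to be estimated in subgroups defined by treatment received, and such estimates would be confounded by prognosis. The expected direction, with intensive pathways looking worse and lighter ones better, rests on one premise: that participants with a poorer outlook are more often routed to more intensive care. The routing rules in the Intervention and Discontinuation sections point that way.

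The size is not determined by the protocol. Under the stated assumptions it ranges from none (no selection) to apparent rate ratios of 1.30 and 0.85 where the truth is 1.00. These are illustrations and not predictions.

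The point does not extend to symptom severity measured at baseline, to indication of treatment if recorded before randomisation, or to the 2-A/2-B split expressed as diagnosis status. The primary intention-to-treat analysis and the gated test of self-efficacy are unaffected.

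**What to change.** In the analysis plan, replace 'type of treatment' as a subgroup variable with variables fixed before allocation in both arms:

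- ICD-10 diagnosis versus subclinical symptoms, which carries the 2-A/2-B distinction
- baseline sickness-absence stratum (below 21 days versus 21 days or more)
- baseline PHQ-9 stratum (10 or below versus above 10)
- indication of treatment, provided it is recorded before randomisation. This needs confirming, because the Module 1-A list places the treatment recommendations after the randomisation step.

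Test each by a treatment-by-subgroup interaction in the existing outcome model and present it as exploratory. Report outcomes by module or care received descriptively only, labelled as non-randomised comparisons.

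The cost is a change of wording before database closure. Diagnosis status is assessed in everyone before allocation, and the two strata are already needed for randomisation. Recording the indication before randomisation may require a check of the order of entry in the case report form. The only loss is a comparison that could not be interpreted as a treatment effect.

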### Monitoring

#### Data monitoring

An independent data monitoring committee (DMC) will be established composed of two clinical professionals and one biometric professional. The DMC will be regularly informed about the course of the trial and all safety issues. Furthermore, the DMC will be asked for advice whether to continue, modify or stop the trial.

#### Harms

Occurrence of adverse events will be documented. Although adverse events are rare during psychotherapy [78], they cannot be completely ruled out. Adverse events may include lack of treatment results, occurrence of new symptoms, increasing symptoms, strains in therapist-patient relationship, strains or changes in work, family or other social relationships, stigmatisation and development of pathological dependency to the therapist [79–81]. In case of adverse events, the psychotherapist and possibly supervisors will weight up further treatment needs as described under *Discontinuation and Modifications of the intervention protocol*. Furthermore, measures will be taken to avoid adverse events including i) the educational programme for psychotherapists to increase awareness of adverse events, ii) supervision of psychotherapists and iii) progress monitoring as described by Rozental [82].

### Formative evaluation

A formative evaluation of the intervention using qualitative methods will be realised. Data will be collected in focus groups and individual interviews. The focus groups and interviews will be recorded and transcribed.

First, prior to the intervention, two focus groups (approximately eight participants per group) are conducted with a) health care professionals and b) employees who have experience with psychotherapeutic consultation and return to work. These focus groups will be analysed using qualitative content analysis with regard to expectations of the participants, facilitating and hindering factors related to early prevention in company settings and future implementation of the intervention.

Second, four narrative focus groups (approximately eight participants per group) will be conducted with a) organisational and b) external experts in the RTW process before and after the implementation of the intervention. The focus groups will be analysed using qualitative content analysis. Expectations of the intervention, facilitating and hindering factors as well as valuation of the intervention will be examined. In addition, knowledge and handling of mental illness will be reconstructed.

Third, a subsample of 20 participants of the intervention group will be questioned in individual narrative interviews at two time points: at the end of the intervention and approximately 6 months later after (gradual) RTW. In more detail, the following subsamples of participants will be interviewed:
Up to six participants who only received module 2-A and/or 3Up to five participants who received module 2-A as well as outpatient or in patient acute treatment and module 3Up to five participants who received module 2-A, vocational rehabilitation as well as module 3Up to four participants who only received module 2-B.

In addition, five participants of the control group will be narratively interviewed 6 months after returning to work. All individual interviews will be analysed using the Documentary Method of Interpretation [83]. This method not only allows to identify reflexive knowledge, but above all to reconstruct tacit knowledge, knowledge of action and experiences. Participants’ expectations of the intervention, experiences and behaviour in the process of intervention, as well as the effect of the intervention on RTW will be reconstructed. In addition, interactions between intervention modules and contextual conditions as well as facilitating and hindering factors will be analysed. Furthermore, effects of the intervention on self-management and self-efficacy as well as the valuation of the intervention by the participants will be examined.

Fourth, based on an overarching case comparison, similarities and differences will be identified in focus groups and individual interviews (referring to the interest in knowledge as mentioned above). The comparison allows evaluation of the intervention beyond the individual case. In summary, the formative evaluation aims to identify facilitating and hindering factors concerning the various intervention modules and in relation to different contextual conditions such as company size and structure.

## Discussion

Worldwide, a treatment gap for CMDs has been described [5, 6]. Inadequate and late treatment may increase the risk of chronicity of CMDs [84] and therefore might contribute to long and recurrent sickness absence and premature retirement [3, 4]. The workplace and its working conditions may contribute beneficially or adversely to the development of CMDs [85–87]. At the same time, the workplace might function as a setting to enable utilization of mental health care interventions by reaching a high number of individuals suffering from CMDs [12].

This study protocol therefore describes a multicentre RCT, which aims to test psychotherapeutic consultation at work. In this study, psychotherapeutic consultation at work consists of a tailored, module-based and work-related psychotherapy. It especially aims to reach patients at early disease stages as well as patients with subclinical symptoms [17]. Due to long waiting times for psychotherapeutic offers in the German health care system [10], we expect that patients of the control group are treated at later time points. We therefore expect that they also report more days of sickness absence than patients of the intervention group. Besides disorder-specific psychotherapy, the intervention group will also receive work-related psychotherapy and elaborate cooperation between mental health care actors. Consistent with previous research [19, 20, 22, 37, 88], those aspects may result in additional reduction of sickness absence in the intervention group. In case that the intervention is shown to be effective to reduce sickness absence and referring to the high prevalence and burden of disease of CMDs [1, 2], implementation of psychotherapeutic consultation at work into practice could have large public health relevance.

If the intervention is shown to be effective to reduce days of sickness absence, we expect that direct and indirect costs related to CMDs are reduced. An additional health economic evaluation will therefore be performed to test whether the intervention is actually cost effective. Previous health economic evaluations of similar interventions [16, 20] may raise expectations of a positive evaluation. In this case, implementation of psychotherapeutic consultation at work might be of economic relevance by relieving financial pressure on health and pension insurances and reducing costs related to loss of productivity due to CMDs.

In Germany, large-scale implementation of psychosomatic consultation at work might be realized by joint financing by health and pension insurances. In accordance with German Social Law, module 1 and 2 might be financed by health insurances as special forms of health care (§140a SGB V) and module 3 might be financed by the German pension insurance as employment participation benefits (§49 SGB IX). Besides publication of research results in international research journals, a manual of the intervention will be developed and made available to the public to support implementation of psychotherapeutic consultation at work into practice.

